### Data Collection and Management

The study data will be collected and managed using REDCap electronic data capture tools hosted at the IRCCS San Raffaele Roma Hospital and Casa di Cura del Policlinico Hospital [62,63]. REDCap is a secure web-based software platform designed to support data capture for research studies, providing (1) an intuitive interface for validated data capture, (2) audit trails for tracking data manipulation and export procedures, (3) automated export procedures for seamless data downloads to common statistical packages, and (4) procedures for data integration and interoperability with external sources.

### Ethics Approval

The ethics committees of both involved centers (ie, IRCCS San Raffaele Roma Hospital and Casa di Cura del Policlinico Hospital) reviewed and approved the study protocol (Ethics Committee IRCCS San Raffaele Roma: protocol code RP05/2018; Ethics Committee Milano Area 2: protocol 705_2018bis).

The institutional review boards of both centers approved the study and will receive study reports at the middle and end of the study and monitor the study implementation and data collection.

Any deviations from the protocol will be promptly notified to the ethics committees and will be applied only after approval.

This study will be conducted in accordance with the principles of the Declaration of Helsinki. Written informed consent forms will be obtained from each participant before the start of the study. Only those participants who provided informed written consent before starting will be included. During the study, written data will be stored in a closed cabinet; all data, after anonymization, will be entered into a REDCap electronic data capture repository. The input data will be double-checked by another research assistant. Personal data will be discarded after 5 years.

The results of this study will be disseminated through peer-reviewed journals and national and international academic conferences only by the professionals directly involved in the clinical trial.

### Patient Withdrawal Criteria

Patients will be informed of the possibility of interrupting the study at any time they deem appropriate. Any interruption will be fully documented in the case report form by the investigators. The investigators shall make all reasonable efforts to maintain the patients who express a willingness to interrupt the participation in the study protocol.

Patients may prematurely discontinue the study if any of the following conditions occur:

Request from the patient, even if not motivatedWithdrawal of consent by the patient to participate in the studyModification of the psychophysical state of the patient, significantly altering at least one of the variables considered in the inclusion or exclusion criteriaThe occurrence of serious adverse reactions, which in the opinion of the investigator, make the continuation of the study impossibleAbsence from >3 consecutive experimental sessionInability of the patient to continue the study for organizational and personal reasons

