## Methods

### Overview

A randomized, parallel-arm, controlled, outcome measurer–blinded, and multicenter clinical trial conducted in 2 neurorehabilitation centers in Italy aims to investigate the effectiveness of AOT in patients with chronic stroke (ie, >6 months from the first event) using quantitative EEG biomarkers, confirming the translational power of a tailored treatment.

A total of 60 individuals who have been enrolled will be randomized to the experimental group in hospital (EG@Hosp), experimental group at home (EG@Home), or control group (CG) in a 1:1:1 ratio.

The EG@Hosp will observe and execute ADL that are task-oriented actions (AOT protocol); the EG@Home will observe and perform the same ADL at home (AOT protocol at home); and the CG will not observe any motor task videos (but will watch video only on landscapes and historical issues), and after verbal instructions, they will perform the same actions observed by the other 2 groups.

After completing the patient screening, randomization will be performed before the first treatment session (T0). At baseline (T0), midintervention (after the 7th session; T1), and after the intervention (15th session or 5th week; T2), outcomes (ie, clinical scales, EEG and electromyography [EMG] signals, and kinematic parameters) will be assessed to evaluate impairment and functional abilities.

For each group, the total duration of the intervention will be 5 weeks (3 times a week) for a total of 15 sessions. After the end of the intervention, a 2-month follow-up assessment period (T3) will be scheduled to assess the maintenance and long-term effects.

The primary outcome assessed at T2 will be assessed by the Fugl-Meyer Assessment-Upper Extremity (FMA-UE) scores.

The trials will be performed at 2 neurorehabilitation centers in Italy: IRCCS San Raffaele Roma Hospital in Rome and at Casa di Cura del Policlinico Hospital in Milan.

All the data will be recorded in electronic case report forms through the REDCap (Research Electronic Data Capture; Vanderbilt University) system, accessed on the web via the internet for data collection and management.

A specific route diagram is presented in Figure 1. The protocol for this study was developed in accordance with the Standard Protocol Items: Interventional Trial Recommendations guidelines (SPIRIT) [40].

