**Inclusion criteria**
First ever unilateral ischemic stroke in the chronic stage (ie, the time elapsed from the event>6 months) provoked a clinically evident upper limb or hand deficit that affects the daily activitiesDiagnosis verified by brain imaging (magnetic resonance imaging)Aged 18-85 yearsCognitive function sufficient to understand the experimental instructions (Mini-Mental State Examination Score of≥24)Chedoke-McMaster Stroke Assessment Scale—arm-hand section score of>1

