### Blinding

Participants and intervention delivery facilitators cannot be blinded to group allocation. Evaluators conducting the clinical, neurophysiological (EEG and EMG), and physical (kinematics) assessments will be blinded to group allocation.

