### Sample Size

As the changes in the effects of upper limb AOT in patients with stroke on EEG biomarkers have not been previously investigated, we have estimated the sample size based on previously published studies [58,59], comparing AOT and conventional therapy. We estimated the sample size required to detect differences in the effects of “group”×“time” interactions on primary clinical outcome (FMA-UE).

For this outcome, an effect size of 0.495 [60,61] is expected based on previous studies. Given the expected effect size, a total sample size of 54 will be required for repeated ANOVA with a power of 0.8 and a 2-sided type-I error of 0.05 (number of groups=3 [ie, EG@Hosp, EG@Home, and CG]; number of measurements=3 [ie, T1, T2, and T3]). Therefore, when considering a dropout rate of 10%, we plan to recruit 20 participants for each group (a total of 60 participants) for this study.

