#### Analysis of the Effectiveness

Analysis of the primary outcome (ie, functionality of the affected upper extremity) will be performed using the per-protocol principle. Treatment effects will be compared using a 2-way repeated ANOVA for clinical measurements, considering “time” (3 levels: T0, T1, and T2) as a within-subject factor and “group” (3 levels: EG@Hosp, EG@Home, and CG) as a between-subject factor.

In addition, the percentage of participants who passed the minimal clinically important differences of the FMA-UE will be compared using chi-square tests between the 3 groups.

The mean power across the assessment “time” (ie, T0 and T2) related to the action observation condition will be implemented in a mixed-design ANOVA to evaluate significant changes. A separate ANOVA will be performed to assess power changes in the stimuli selection data, using “treatment” (ie, EG@Hosp vs EG@Home vs CG) as the between-subjects factor and action as the within-subjects factor. To assess the predictive value of biomarkers for AOT effectiveness, an analysis of covariance (ANCOVA) will be performed considering the clinical data as the dependent variable, the “group” as a fixed factor, and the biomarkers as covariates.

Subsequently, to evaluate kinematic parameters recovery, a mixed design ANOVA will be implemented with “time” and “treatment” as within- and between-subjects factors, respectively.

The level of significance will be set at *P*<.05. For post hoc comparisons, the level of significance will be set at *P*<.017 after Bonferroni adjustment (.05/n; the number of comparisons, n=3) for the comparison of interaction effects. Cohen *d* will be calculated to determine the effect size of the change in scores for the behavioral motor outcomes between the groups. Immediate training effects (data from T0-T2) and the durability of training effects (data from T2-T3) will be separately investigated using mixed effect models.

Clinical-neurophysiological correlations will also be analyzed: the correlation between the ERD and factors such as the clinical scale score will be studied. To evaluate the differences in trends related to the clinical evolution of the patients, we will define a new variable to group the participants according to the presence or absence of relevant clinical improvements. The relevant clinical improvement will be defined by a clinical specialist for this purpose.

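### Read literally, the withdrawal criteria make a change in the treated arm function a ground for leaving the study, and the per-protocol primary analysis gives no protection against such loss

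*Protocol article*

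**What the plan says.** All references are to the protocol article.

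- **Patient Withdrawal Criteria.** The list opens with "Patients may prematurely discontinue the study if any of the following conditions occur". One listed condition is a modification of the "psychophysical state of the patient, significantly altering at least one of the variables considered in the inclusion or exclusion" criteria. The section also asks investigators to try to keep patients who want to stop, and to document every interruption in the case report form.
- **Inclusion criteria.** The stroke must have "provoked a clinically evident upper limb or hand deficit that affects the daily" activities. A second arm-function criterion is "Chedoke-McMaster Stroke Assessment Scale—arm-hand section score of>1".
- **Methods, Overview.** "The primary outcome assessed at T2 will be assessed by the Fugl-Meyer Assessment-Upper Extremity (FMA-UE) scores". T1 follows the 7th session, T2 is at the 15th session or 5th week, and T3 is a 2-month follow-up.
- **Analysis of the Effectiveness.** "Analysis of the primary outcome (ie, functionality of the affected upper extremity) will be performed using the per-protocol principle".
- **Blinding.** "Participants and intervention delivery facilitators cannot be blinded to group allocation"; those who carry out the assessments are blinded.

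**The concern.** A withdrawal rule should not be triggered by the quantity the trial is trying to change. Here the trigger is defined by reference to the eligibility variables as a whole, and two of them describe upper limb function. If a patient leaves because arm function changed, and T2 FMA-UE is then missing or left out of the analysis set, the missingness is informative. Loss of marked improvers would lower the mean of the arm they leave, and loss of patients who worsened would raise it. A later analysis plan can decide how to handle such patients, but it cannot recover a T2 score that was never taken. A patient whose arm worsens is also one whose course a safety review would want to see.

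**Working it through.** The point rests on the wording of a rule and not on a stated figure, so the main check sets the sections side by side.

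**1. What triggers the rule.** A change in the patient's state that significantly alters at least one eligibility variable. No direction is given and no variable is exempted. What ends is participation in the study, not only in treatment.

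**2. Which eligibility variables are the treated function.**

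| Variable | Could improvement reach it? | Could worsening reach it? |
|---|---|---|
| Arm or hand deficit affecting daily activities | Yes, if the deficit no longer affects them, or if any significant alteration counts | Only if any significant alteration counts |
| Chedoke-McMaster arm-hand score >1 | It cannot breach the limit, which is a lower bound | Yes, if the score falls to 1 |

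**3. Link to the primary outcome.** FMA-UE is the primary outcome at T2, and the section on upper extremity functionality describes it as an impairment index. It reflects the same deficit.

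**4. What happens to a discontinued patient's data.** The primary analysis is per-protocol, so such a patient would be expected to fall outside it. The article does not say that assessment continues. That silence alone is not a fault in a condensed article, but it means that nothing shown offsets the per-protocol choice.

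**5. Scale.** Let a fraction p of an arm be lost, with mean change m_L, and let the remaining patients have mean change m_R.

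Full-arm mean = (1 − p)·m_R + p·m_L. Observed mean = m_R. Shift = p·(m_R − m_L).

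With 20 per arm (Sample Size), one loss gives p = 1/20 = 0.05 and two give p = 2/20 = 0.10. The shift is 5% or 10% of the gap between lost and retained patients. The document gives neither p nor the gap. The dropout allowance (60 − 54 = 6 patients, or 2 per arm) restores numbers but does not remove bias.

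**6. Whether 0.495 can serve as a yardstick.** The Sample Size section says "an effect size of 0.495 [60,61] is expected based on previous studies" without naming the metric. For the group-by-time interaction with 3 groups and 3 measurements, df1 = 2 × 2 = 4 and, at N = 54, df2 = (54 − 3) × 2 = 102. The stated 54 comes out under more than one reading:

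- Cohen's f, with λ = f²N = 0.495² × 54 = 13.23: power 0.825.
- Standardised difference between the extreme arms, f = 0.495·√(1/6), with λ = f²·N·3/(1 − ρ) and ρ = 0.5: the same λ of 13.23, power 0.825.
- Standardised difference of two equal AOT arms from control, f = 0.495·√2/3, with ρ = 0.3: power 0.804.

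Under the first reading, with two equal AOT arms, the corresponding mean difference would be 0.495 × 3/√2 = 1.05 SD, about twice 0.495. The metric cannot be settled from the document, so a bias in SD units should not be set beside 0.495.

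**The case against.** The case for leaving the rule alone is substantial.

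- **Permissive wording.** The rule says that patients may discontinue, and the same section asks for efforts at retention, although only for patients who themselves want to stop. This stands: the rule allows loss and does not require it.
- **Probable intent.** The condition speaks of the psychophysical state and stands beside serious adverse reactions and missed sessions. The exclusion criteria offer natural targets, such as cognitive impairment and severe medical problems. Intercurrent change is the likely meaning, but the text does not limit the rule to it.
- **Thin route for improvers.** The Chedoke-McMaster limit cannot be breached by improvement, and a deficit present for more than 6 months is unlikely to resolve within 5 weeks. This stands and makes the problem rare.
- **Few occasions to apply it.** Chedoke-McMaster is not among the listed outcome scales, and T1 is the only scheduled assessment between baseline and T2. A patient found changed at T2 has already given the primary outcome. This narrows the exposure further, although T3 could still be lost.

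Two stronger readings are tempting. A reader might infer that unblinded investigators apply the rule. The Blinding section names participants and those who deliver the intervention as unblinded, and no section says who applies this criterion. A reader might also put a number on the bias by trimming one tail of one arm: for normal change scores, losing the top 5%, 10% or 20% lowers the mean by 0.11, 0.195 or 0.35 SD. Nothing in the document supports that pattern of loss.

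**Conclusion.** The point holds in a limited form. As worded, the withdrawal criteria reach the treated arm function, and the stated per-protocol primary analysis does not protect the T2 FMA-UE comparison from outcome-dependent loss. The conclusion assumes that the rule is read as written and that discontinued patients fall outside the per-protocol set. Few patients are likely to be affected. The size and direction of any bias cannot be derived from the document, and the document does not show that responders or deteriorators are in fact removed. The correction is worth making because it is cheap and because one or two outcome-related losses are not negligible with 20 patients per arm.

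**What to change.** 1. Reconcile the inclusion criteria, the withdrawal criteria and the primary analysis. The sponsor should decide and state whether a change in the treated arm function falls under this criterion. That clinical decision is the sponsor's.
2. For any patient discontinued under the criterion who has not withdrawn consent, collect the scheduled FMA-UE at T2 and T3 and include it in an analysis of all randomised patients, reported with the per-protocol one.
3. Report each use of the criterion by arm, with reason and date, from the interruptions already documented in the case report form.

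The cost is a little more data collection at visits already scheduled and one further analysis, with no additional patients. The abstract says that recruitment closed in December 2022. For patients already past T2 or T3, step 2 can use only scores already recorded; step 3 remains possible for all.

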## Results

Participants will be identified from hospital records or among those who show interest in participating by seeing the initiative through the communication channels of the hospitals, posters, and networks; all of them will be contacted by phone. After obtaining permission, the physicians will visit and explain the study. If they agree, the research assistants will manage their recruitment. This will be performed every week to identify participants.

The results of the evaluations will be released to the participants upon request. The results of this study will be presented at national and international patient organizations and to the general public.

The study protocol is part of a project (project code GR-2016–02361678) approved and funded by the Italian Ministry of Health.

## Discussion

### Rationale

The rationale of this study protocol is based on the AOT in patients with chronic stroke for upper limb rehabilitation. AOT relies on the MNS network to boost motor functions in patients affected by motor impairments, engaging the brain networks active during action execution. The imitation of observed gestures may increase the reorganization of the primary motor cortex, contributing to the formation of motor memories of the observed action, thus improving the physiological processes underlying motor learning [28,30].

It is well known that the MNS plays an essential role in considering the actions of others and in our ability to learn by imitation [64]. Furthermore, the activation of motor areas by AOT seems to be reinforced by the subsequent active execution of observed actions [9]. Indeed, as a motor representation technique, AOT has become an emerging motor learning training strategy to improve motor recovery in different healthy and pathological populations. Moreover, AOT preactivates specific areas of the brain, reinforcing intact cortical networks and facilitating the activation of the damaged ones [65]. Recently, a systematic review on this topic highlighted how AOT is an effective method for improving upper limb motor functions after stroke and that task-based AOT (based on goal-oriented activities, eg, a reaching task) might be superior to movement-based AOT (eg, a pure movement of elbow extension without any functional goals), as mirror neurons are more receptive to object-related actions [24]. The authors concluded that the optimal dosage, substantiality of effects, and underlying neural mechanisms of AOT in improving upper limb motor functions in patients with stroke should be considered in further investigations [24]. According to previous findings, we believe that increasing evidence supporting the effectiveness of observation-based inventions to assist traditional therapeutic practice in the rehabilitation of motor disorders [66] must be explored.

On the basis of these findings, the proposed study protocol aims to identify the effects of AOT and motor rehabilitative treatment on the clinical and functional status of patients with stroke through an advanced multidomain assessment and to infer the effects on brain plasticity.

This study will be a starting point for the evaluation of the effectiveness of the 2 AOT scenarios proposed (ie, AOT in the hospital and AOT at home) in patients with chronic stroke (ie, the time elapsed from the event is >6 months), as well as for the assessment of the predictive value of neurophysiological biomarkers.

Specifically, we will attempt to induce functional modification of the cortical components by exploiting the features of the MNS, demonstrating relevant clinical, kinematic, and neurophysiological changes after AOT.

The added value of a multidomain assessment that includes test and clinical scales and kinematic and neurophysiological (ie, EEG and EMG) outcomes aims to identify neurophysiological biomarkers capable of evaluating the effectiveness of AOT and confirming the translational power of a tailored rehabilitation treatment for chronic stroke.

Moreover, as AOT is involved in the motor learning process and could be a useful addition to conventional therapy, an innovative home-based AOT program will be implemented in the framework of this protocol study. Indeed, the continuity of care and personalized rehabilitation for people who are affected by chronic diseases is often interrupted after transitioning from the hospital to the home environment [67].

### Future Implications

As a result of the COVID-19 pandemic, telerehabilitation and home care are growing rapidly, offering opportunities for integrating digital health interventions into community-based aging services. The COVID-19 pandemic has accelerated the adoption of technology and virtual care in patients’ homes, and this trend likely to stay after the pandemic. Although notable age differences in technology use remain, the adoption of key technologies by older adults is the new challenge. With this purpose, this study protocol will permit the investigation of whether a home-based program could be effective, especially in terms of exercise capacity and perceived ease of use, offering comparable benefits to hospital-based programs.

The translational research results will ensure advances in the optimization and personalization of the rehabilitative process, both in hospitals and at home, thus improving upper limb motor functions and the quality of life of patients with chronic stroke.

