The encouraging results obtained from clinical outcomes were confirmed by studies that included instrumental assessments, among others: AOT has an additional positive impact on modifying cortical activation patterns [9,26,38] and in improving upper limb kinematics [39].

Furthermore, in Italy, to the best of our knowledge, no evidence has been found related to the effectiveness of home-based AOT programs compared with the same AOT performed in the hospital.

According to the inspiring results reported in the literature, AOT rehabilitative treatment exemplifies a translational step from neuroscience to clinical rehabilitation applications.

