### Aims

The project aims to achieve the following objectives: (1) induce functional modification of the cortical components underpinning the action organization, exploiting the peculiar features of the MNS and demonstrating the relevant clinical, kinematic, and neurophysiological changes after AOT—in particular, the analysis of the AOT effectiveness will also consider the predictive value of neurophysiological biomarkers; and (2) provide the home-based AOT program, to the best of our knowledge, for the first time in Italy, thereby rendering evidence-based considerations regarding the feasibility and impact of our home-based AOT program for future systematic application of the approach.

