#### AOT Protocol for EG@Home

After appropriate training of patients and caregivers, the use of tablets will allow home-based treatment. In particular, a tablet will be enabled with a web-based program that will be used to train the patients (and receive feedback on their progress).

Participants enrolled in EG@Home will be asked to carefully observe the videos showing different daily actions on the tablet. The web-based program will present each motor act for 2 minutes. At the end of each motor act presentation, the web-based program will ask the participants to execute the observed motor sequence for 1 minute (by audio or video message) with the affected upper limb.

Participants enrolled in EG@Home will perform rehabilitation treatment at their homes.

A 7-inch tablet with Android software 11.0 will be used for the experimentation. Before handing the tablet to the patient, the researcher will schedule the AOT program via the web, defining the days when the patients should perform the treatment independently at home. Patients can check the days on which treatment will be performed by consulting the web-based application, specifically the section where the scheduling of sessions is provided, on the tablet. The research teams will be remotely monitoring the progress of the EG@Home sessions using a dedicated web platform.

The web-based application was developed by a specialist following the researchers’ specification.

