#### Usability of the Platform (Only for Home-Based Treatment)

The feasibility of the home-based treatment and the usability of the platform, as well as the participants’ satisfaction with the services, will be assessed by patients at the end of the intervention (T2) with the following scales:

TAM [57] includes 3 criteria (perceived ease of use, perceived usefulness, and behavioral intention to use). A Likert scale has been developed in which the user will rate from 1 to 7 whether they agree with a series of statements.Nonstructured interviews (adapted from the TAM) to investigate patients’ feelings.

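### Feasibility of the home programme is a stated aim but is measured only by an acceptance questionnaire and interview at T2; secondarily, the planned difference tests cannot show comparability with hospital AOT

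*Protocol article*

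**What the plan says.** **Feasibility.** The second aim includes "rendering evidence-based considerations regarding the feasibility and impact of our home-based AOT program" (Aims), and the abstract's Objective and Conclusions repeat it. The section on usability of the platform states how it is measured: feasibility, usability and satisfaction "will be assessed by patients at the end of the intervention (T2) with the following scales". The two instruments that follow are the TAM (ease of use, usefulness, intention to use) and a nonstructured interview adapted from it.

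Two other sections describe relevant data that are not named as feasibility outcomes. The home protocol says "The research teams will be remotely monitoring the progress of the EG@Home sessions using a dedicated web platform". Patient Withdrawal Criteria requires interruptions to be documented in the case report form, and lists repeated absence from sessions, patient request and organisational reasons among the conditions for leaving early.

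**Home versus hospital.** The Background names as an evidence gap in Italy the "effectiveness of home-based AOT programs compared with the same AOT performed in the hospital". Future Implications says the study will permit investigating whether a home programme could be effective, "offering comparable benefits to hospital-based programs". The Sample Size section is framed for difference: "We estimated the sample size required to detect differences in the effects of" the group-by-time interaction on FMA-UE. The primary analysis is per protocol: a repeated-measures ANOVA, with post hoc tests at P<.017 "after Bonferroni adjustment (.05/n; the number of comparisons, n=3) for the comparison of interaction effects". The same section also plans Cohen d between groups, a three-group chi-square on the proportion passing the FMA-UE minimal clinically important difference (MCID), and mixed effect models.

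**The concern.** Feasibility of a self-run home programme depends first on whether patients do the sessions and stay to the end. The TAM and the interview ask something else: whether the user finds the system easy and useful and would go on using it. They are also taken at T2, when patients who gave up may no longer be there to answer. Missing answers would then come mainly from those for whom the programme did not work, and the bias would favour the home programme. The aim mentions future systematic use of the approach, so this matters.

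The comparability question has a related weakness. A test of difference that comes out non-significant in a small trial is compatible with no loss and with a material loss. Without an interval and a rule for reading it, the result cannot answer the question that the Discussion raises.

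**Working it through.** **1. Feasibility: the sections side by side.**

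- Aim: feasibility and impact of the home programme (Aims).
- Measures: TAM and interview, answered by patients, at T2 (Usability of the Platform).
- Who may be missing: patients who discontinue before T2 (Patient Withdrawal Criteria).
- Data that would show completion: web-platform monitoring (AOT Protocol for EG@Home) and documented interruptions (Patient Withdrawal Criteria). Neither is listed as a feasibility measure.

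Precision of the missing measure: 20 patients are to be randomised to EG@Home. For illustration, if 16 of 20 were retained (80%), the exact 95% CI would be 56% to 94%; for 14 of 20 (70%), 46% to 88%. The estimate is imprecise, hence the need for an interval.

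**2. The plan's own sample size.** Inputs from Sample Size: "an effect size of 0.495 [60,61] is expected based on previous studies", 3 groups, 3 measurements, power 0.8, two-sided alpha 0.05. The metric of 0.495 is not named; reading it as Cohen f reproduces the stated total.

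- Noncentral F for the interaction: λ = f²N, df1 = (3−1)(3−1) = 4, df2 = (N−3)(3−1).
- N = 51: power 0.798. N = 52: power 0.808. N = 54, the smallest balanced total reaching 80%: λ = 0.245 × 54 = 13.2, power 0.825.
- Dropout: 54 / 0.9 = 60, or 20 per arm with 18 evaluable.

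The stated 54 and 60 are reproduced, as the size for a test of difference across three groups.

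**3. What 18 per arm gives for home minus hospital.** The documents give no FMA-UE SD, so results are in units of the SD at T2. They give no T0–T2 correlation r, so a range of 0.5 to 0.9 is assumed.

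- Unadjusted 95% half-width: t(.975, 34) × √(2/18) = 2.032 × 0.333 = 0.68 SD.
- Adjusting for T0 multiplies the SD by √(1 − r²): 0.866 at r = 0.5, 0.600 at 0.8, 0.436 at 0.9.
- Miss rate: probability that a two-sided test at .017 is non-significant when home is truly 0.5 SD worse (noncentral F with 1 and 34 df, noncentrality d²·18/2, d = 0.5 / √(1 − r²)).

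| Analysis | 95% CI half-width (SD) | d | Missed at .017 |
|---|---|---|---|
| Unadjusted T2 | 0.68 | 0.50 | 83% |
| T0-adjusted, r = 0.5 | 0.59 | 0.58 | 77% |
| T0-adjusted, r = 0.8 | 0.41 | 0.83 | 50% |
| T0-adjusted, r = 0.9 | 0.30 | 1.15 | 18% |

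The planned ANOVA includes T0, so its contrast is closer to the adjusted rows. For simple change scores the SD factor is √(2(1 − r)), and the miss rate is 55% at r = 0.8 and 20% at r = 0.9.

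**The case against.** **On comparability.** The quoted phrase is a hedged sentence under Future Implications. Comparability is not among the formal aims, and the article calls the study a starting point. A reader might infer that the trial will declare home AOT comparable whenever the post hoc test is non-significant; no section states such a rule. A reader might also infer that this post hoc test is the only home-versus-hospital analysis. It is not: Cohen d, the MCID-responder comparison and mixed models are planned too. Nor does the 83% describe the planned analysis, which uses T0; with a high correlation the miss rate falls to 18%. Finally, 0.5 SD cannot be called clearly worse, because the article gives neither an SD nor an MCID value.

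All of this stands, and it makes comparability the secondary point. What remains is that every stated analysis is a difference test or an estimate without a stated interval. An interval rule could be in a fuller document, but the sample size and tests given here are explicitly for differences.

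**On feasibility.** T2 is defined by the 15th session or the fifth week, so a patient who stops sessions may still reach it by calendar. Nothing says that early leavers will not be asked. Interruptions are documented and sessions are monitored, so abandonment would be on record. There is also no threshold for declaring feasibility.

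This rules out the stronger claims that early leavers are certainly excluded, or that a largely abandoned programme would be declared feasible. It does not change which measures the article assigns to feasibility: two, both of acceptance. This is a stated choice of measures, not a detail left open.

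**Conclusion.** The feasibility point holds and is the main one. A stated aim is tied to measures of acceptance at T2, while completion and retention, for which sources exist, are not named as outcomes. The result could look better than the programme is, if early leavers are numerous and do not contribute; how many there will be cannot be judged from the article.

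The comparability point holds as a limit on interpretation. With 18 per arm, the 95% CI reaches 0.68 SD either side of the estimate unadjusted, and 0.59 to 0.30 SD with T0 adjustment. A 0.5 SD deficit is missed 83% of the time unadjusted, and 77% to 18% adjusted. These figures assume equal SDs, 18 evaluable patients in each arm and a correlation between 0.5 and 0.9, none of which the article verifies. The 0.5 SD deficit is illustrative. The documents do not support saying that non-significance is the likely result in every case; that depends on the correlation.

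**What to change.** **Feasibility.** In the section on usability of the platform, add two feasibility outcomes beside the TAM and the interview: sessions completed out of 15, and retention to T2. Define both for all patients randomised to EG@Home, take them from the web-platform monitoring and the case report form, and report each with a 95% CI.

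**Home versus hospital.** Report EG@Home minus EG@Hosp on FMA-UE at T2, adjusted for T0, with a 95% CI, in all randomised patients as well as per protocol. State that a non-significant difference will not be read as comparable benefit, and that the result will be called inconclusive when the interval still includes a clinically relevant loss. The size of that loss should be justified as a between-group difference. The MCID in the analysis section is used to classify individual participants, and adopting it unexamined as a margin between arms would be debatable.

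**Cost.** No additional patients are needed. The completion data should come from monitoring and documentation already planned, and the rest is analysis and wording, provided T2 outcomes are available for patients outside the per-protocol set. The main downside is that comparability will probably be reported as inconclusive, and the feasibility rates will have wide intervals with 20 patients.
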